## Abstract

**Background:**

Physical inactivity represents a significant public health issue with substantial socioeconomic costs. In the autonomous Community of Madrid, 39.17% of the population does not meet the World Health Organization recommendations for physical activity (PA). Gender, sex, and occupational factors are well-established determinants of leisure-time physical activity (LTPA); yet, few studies have examined these factors among university staff.

**Objective:**

This study aims to analyze the relationship between LTPA and work ability among university staff in the autonomous Community of Madrid, considering the potential modifying effect of occupational PA. Secondary objectives include examining associations between LTPA, musculoskeletal disorders, health-related quality of life, physical and mental workload, and working conditions, with a focus on sex and gender differences.

**Methods:**

A cross-sectional study was designed involving 885 university staff members from the University of Alcalá, Madrid, Spain. Participants will complete an online survey, including sociodemographic questions and validated instruments: the Global Physical Activity Questionnaire, Work Ability Index, Nordic Musculoskeletal Questionnaire, Short Form-12 Health Survey, and the National Aeronautics and Space Administration Task Load Index. Descriptive and inferential statistics will be performed to assess the associations between LTPA, occupational PA, and work ability, adjusted for relevant covariates.

**Results:**

This study was approved by the ethics committee of the University of Alcalá in November 2024. Recruitment began in December 2024 and will continue until June 2027. Data analysis will be conducted progressively. Results will be disseminated in peer-reviewed journals and presented at scientific conferences following gender-sensitive and transparent reporting standards.

**Conclusions:**

Understanding the determinants of PA and their interaction with work ability and gender may inform the development of targeted, culturally sensitive interventions to reduce sedentary behavior and its associated health and economic burdens in university staff.

**Trial Registration:**

ClinicalTrials.gov NCT06723808; https://clinicaltrials.gov/study/NCT06723808

**International Registered Report Identifier (IRRID):**

DERR1-10.2196/80298

## Introduction

### Background

Physical activity (PA) is widely recognized as a cornerstone of public health due to its proven effectiveness in preventing and managing noncommunicable diseases [1]. However, PA has emerged as an escalating global health and socioeconomic challenge [2], significantly impacting the Spanish population, particularly in the autonomous Community of Madrid (CAM), where more than 39% of the adults fail to meet World Health Organization (WHO) guidelines [3]. In occupational contexts, this is especially concerning due to the negative association between inactivity and work ability, a key predictor of productivity, employment sustainability, and healthy aging in the workforce [4,5].

PA can be classified into different domains, with leisure-time physical activity (LTPA) and occupational physical activity (OPA) being particularly relevant in work-related health research [6,7]. OPA refers to the physical effort involved in work-related tasks [8], whereas LTPA encompasses voluntary activities, such as exercise, sports, and recreation [6]. Although both contribute to total PA, their effects on health are not equivalent [4,6-9].

Substantial evidence links high levels of LTPA with enhanced overall health, lower risk of noncommunicable diseases, and improved mental and musculoskeletal health [1,9]. Conversely, high OPA levels have been associated with increased risks of musculoskeletal disorders (MSDs) [10], cardiovascular diseases [10,11], and higher mortality rates. This apparent contradiction, referred to as the “PA paradox,” highlights that OPA often lacks sufficient intensity, involves prolonged durations without recovery, and typically occurs under low-autonomy conditions [11]. This paradox provides a relevant conceptual framework for this study, reinforcing the importance of examining LTPA and OPA as distinct domains with potentially divergent effects on work ability.

Moreover, while LTPA has been shown to positively influence occupational outcomes, including work ability [12], reduced absenteeism [13,14], greater job satisfaction [15], improved performance, and higher productivity [16,17], an imbalance between OPA and LTPA may lead to diminished functional capacity, increased absenteeism, and an elevated risk of burnout [11-13,17-21].

Although international guidelines, such as those issued by the WHO, define minimum PA thresholds for various age groups and conditions [20], social determinants of health, including gender, sex, socioeconomic status, and workplace environment, play a significant role in shaping individuals’ ability to meet these recommendations [22-29]. In this context, unequal access to LTPA opportunities contributes to the persistence of health disparities [20,21].

Gender and sex play a particularly important role in shaping PA behavior and work-related outcomes. Women tend to engage in less LTPA than men, a pattern observed in Spain and the CAM region, where 46.89% of the women report being sedentary compared to 30.61% of the men [3]. This disparity is likely driven by a combination of gender- and sex-related factors. Gender-based determinants may include unequal caregiving responsibilities, reduced time for leisure due to social roles, and cultural expectations regarding self-care and productivity, which can limit women’s participation in LTPA [22,23,30]. In contrast, sex-related factors, such as menopause, endometriosis, and urinary incontinence (biological or physiological processes specific to female reproductive health), may directly impact physical capacity and perceived work ability [24]. These distinct but intersecting influences are often overlooked in occupational health research, highlighting the need for a gender-sensitive and sex-aware approach.

MSDs further complicate this picture, as they are among the most prevalent occupational health issues in Europe and have been consistently linked to reduced work ability and quality of life [25-28]. Given their potential association with both PA levels and occupational demands, they represent a relevant outcome for understanding the interplay between LTPA, OPA, and workforce health. University staff represent a highly relevant study population given their exposure to elevated cognitive and sedentary workloads as well as their strategic role within knowledge-based economies. The university setting also provides a distinct methodological advantage, encompassing diverse occupational profiles with markedly different levels of OPA. PDI (Personal Docente e Investigador): Teaching and Research Staff, PI (Personal Investigador): Research Staff (not Principal Investigator), PTGAS (Personal Técnico, de Gestión, de Administración y de Servicios): Technical, Management, Administrative, and Services Staff often perform duties involving higher levels of physical effort. This internal heterogeneity allows for the examination of different domains of PA and work ability within a single institutional context, making it particularly well-suited for exploring the PA paradox.

Although physical fitness and higher LTPA levels have been associated with greater work ability and fewer musculoskeletal concerns [14,29,31], much of the existing literature does not adequately distinguish between OPA and LTPA or focuses predominantly on male or younger populations [13,32]. Furthermore, limited attention has been given to the role of sex and gender in moderating these relationships as well as the broader influence of social determinants of health, such as sex, gender, and occupational context, on PA behaviors and work-related outcomes [33-40]. Therefore, further research is needed to examine the interplay between LTPA, OPA, and work ability, incorporating a gender perspective and accounting for the influence of the social determinants of health. Such knowledge is critical to informing the development of healthy, equitable, and sustainable work environments.

### Objectives

On the basis of the aforementioned background, the primary objective of this study is to analyze the relationship between LTPA and work ability among university staff in the CAM, considering the potential modifying effect of OPA, and exploring differences by sex and gender. The secondary objectives are to (1) determine the prevalence of MSDs in this population and analyze their association with LTPA and OPA levels using validated questionnaires; (2) evaluate the relationship between both domains of PA and perceived physical and mental workload, adjusting for occupational role and sociodemographic factors; (3) examine the association between LTPA and OPA and self-perceived health-related quality of life (HRQoL); and (4) explore whether these associations vary according to sex, gender, and occupational category.

## Methods

### Study Design

This is a descriptive, cross-sectional, population-based study with a gender perspective. The study was registered on ClinicalTrials.gov before data collection (NCT06723808).

### Study Population and Setting

The study population consists of university staff working in the CAM. A representative sample of 885 workers from the University of Alcalá (UAH), Alcalá de Henares, Madrid, Spain, was selected. Participants include members of the PTGAS, PDI, and PI.

Inclusion criteria are (1) aged ≥18 years and (2) having sufficient proficiency in Spanish to complete study procedures. The questionnaire will be administered exclusively in Spanish, as it is the official and working language in the study setting. Consequently, only participants with adequate Spanish comprehension will be eligible. While this approach ensures the reliability of self-reported data, it may limit the generalizability of the findings to non–Spanish-speaking university staff.

Exclusion criteria include (1) cognitive impairment preventing comprehension of study information or completion of the survey, (2) severe neurological deterioration, and (3) diagnosed severe mental illness preventing the provision of informed consent.

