### Recruitment and Sampling

Due to the institutional data protection constraints, it is not possible to distribute the survey invitation directly to all university employees. Consequently, a multichannel recruitment strategy is being implemented. The study information sheet and participation link are being disseminated via email to deans, faculties, departments, and the human resources department of the UAH, who may forward it to relevant bodies at their discretion. In addition, posters containing QR codes and brief study details are placed on bulletin boards across UAH buildings to increase visibility. Participants are also encouraged to share the study with colleagues to broaden its reach and improve participation rates, thereby introducing a secondary snowball component.

While this strategy incorporates elements of exponential snowball sampling, it is designed to promote broad participation across different occupational roles while complying with data protection policies. This approach facilitates access to diverse occupational profiles and enhances heterogeneity in the study sample.

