### Sample Size

The sample size was calculated for a finite population using Microsoft Excel based on the total UAH workforce (N=3117). A minimum of 796 (25.53%) participants were required to achieve a 95% CI, 3% margin of error, and population proportion of 0.5. This last value was chosen due to the absence of previous prevalence data on the variables of interest, as it maximizes sample size under conditions of uncertainty and ensures sufficient statistical power across all outcomes. Accounting for a potential 10% dropout rate, the final estimated sample size was determined to be 885 (28.39%) participants.

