### Strengths and Limitations

This protocol presents several strengths. First, it uses validated and widely used instruments to assess LTPA, OPA, work ability, and relevant covariates, alongside comprehensive sociodemographic data. The online, self-administered format of the questionnaire reduces potential bias associated with interviewer-led responses and facilitates participation across diverse occupational groups. By collecting key covariates, this study is designed to account for potential confounding factors, ensuring that observed associations are more likely attributable to the primary research objectives. In addition, the estimated sample size provides adequate statistical power to detect significant associations, and the inclusion of participants with varied occupations and occupational demands enhances the generalizability of findings to the broader CAM working population.

The primary limitation of this study is its cross-sectional design, which precludes causal inference between the variables of interest. Longitudinal and interventional studies will be necessary to establish causal relationships and evaluate the effectiveness of tailored PA interventions. In addition, the use of a nonprobability sampling strategy, necessitated by institutional data protection constraints, may introduce selection bias and limit representativeness. However, the multichannel recruitment approach has been carefully designed to promote broad dissemination across occupational groups, and the anticipated heterogeneity of the sample is considered sufficient for the study’s exploratory objectives. Moreover, the use of self-reported measures introduces the possibility of reporting bias, which could affect the accuracy of certain variables. Nevertheless, the use of validated instruments mitigates this concern to some extent. Finally, the absence of objective PA measurements (eg, accelerometers or step counters) may limit the precision of exposure assessment; however, this was a deliberate decision made during the study design phase to prioritize anonymity and feasibility, and it will be addressed in future phases involving subsamples with identifiable data.

As all questionnaire items are mandatory, missing data are not expected. Nonetheless, any unexpected data loss (eg, due to technical issues) will be managed using listwise deletion.

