### Conclusions

This study aims to analyze the relationship between occupational and LTPA and work ability among university staff with diverse occupational demands in the CAM. By incorporating a gender-sensitive perspective, the findings are expected to provide insights into how different domains of PA, particularly leisure time versus occupational, interact with musculoskeletal health, mental and physical workload, and HRQoL.

The methodological design, grounded in validated measurement tools and a representative university population sample, is intended to generate robust and transferable evidence. By including both male and female participants, this study also seeks to address critical gaps in the literature regarding sex- and gender-based differences in the effects of PA and occupational demands.

The results of this research may inform the development of workplace health strategies that promote balanced PA, support sustainable work ability, and prevent noncommunicable diseases in knowledge-based work environments. Moreover, this study has the potential to guide future interventions and public policies aimed at reducing gender-based disparities in occupational health and equitable access to PA, in alignment with global health priorities and the Sustainable Development Goals.

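### The sample is called representative and generalizable to Madrid's workers, but it is self-selected within one university, so the ±3% margin is only nominal

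*Protocol article*

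**What the plan says.** Four statements in the protocol article claim a sample that stands for a wider population:

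- Study Design labels the study population-based.
- Study Population and Setting says "A representative sample of 885 workers from the University of Alcalá (UAH), Alcalá de Henares, Madrid, Spain, was selected". It defines the target more widely than UAH: "The study population consists of university staff working in the CAM".
- Strengths and Limitations says that including varied occupations "enhances the generalizability of findings to the broader CAM working population".
- Conclusions describes the design as "grounded in validated measurement tools and a representative university population sample, is intended to generate robust and transferable evidence".

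Two sections describe how participants are actually obtained:

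- Recruitment and Sampling explains that data protection rules prevent inviting every employee directly. Deans, faculties, departments and human resources receive the link and decide whether to forward it. Posters with QR codes are displayed, and participants are encouraged to share the study. The article says that "this strategy incorporates elements of exponential snowball sampling".
- Strengths and Limitations concedes that "the use of a nonprobability sampling strategy, necessitated by institutional data protection constraints, may introduce selection bias and limit representativeness".

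The Sample Size section takes the UAH workforce of 3,117 as a finite population and gives 796 as the number "required to achieve a 95% CI, 3% margin of error, and population proportion of 0.5", raised to 885 for 10% dropout. The first secondary objective is to determine the prevalence of MSDs in university staff in the CAM.

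**The concern.** The two sets of statements cannot both stand. Nobody is selected in the sampling sense: staff opt in after an uneven and partly unrecorded spread of the invitation, and their inclusion probabilities are unknown. Three populations are also used interchangeably: UAH staff (recruited and sized), university staff in the CAM (the stated study population) and CAM workers in general (the claimed reach).

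A ±3% margin describes random sampling error alone. Beside the word *representative*, it invites readers to take an MSD prevalence from this survey as accurate to 3 points for UAH, or for a wider group. A survey on physical activity, pain and work ability may well attract staff for whom those topics matter, and prevalence is the quantity most directly distorted by that.

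**Working it through.** **Inputs from the Sample Size section.** N = 3,117; 95% confidence (z = 1.96); margin e = 0.03; p = 0.5; minimum n = 796; dropout 10%; final n = 885.

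**1. Reproduce the plan's figure.** For one proportion under simple random sampling from a finite population:

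n = N z² p(1−p) / [e²(N−1) + z² p(1−p)]
= 3,117 × 0.9604 / (0.0009 × 3,116 + 0.9604)
= 2,993.6 / 3.7648 = 795.1, rounded up to 796.

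Dropout: 796 / 0.9 = 884.4, rounded up to 885. Both figures reproduce.

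**2. What the margin refers to.** At n = 796:

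- without finite-population correction: 1.96 × √(0.25/796) = 3.47%
- correction factor: √[(3,117 − 796)/3,116] = 0.863
- product: 3.00%

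The ±3% therefore depends on treating 796 as a random draw of about a quarter of UAH staff. That correction has no meaning for a population larger than UAH.

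**3. How much self-selection uses up 3 points.** Let π be the true prevalence and r the ratio of participation probabilities, staff with MSDs to staff without. Prevalence among respondents is πr / (πr + 1 − π). The article gives neither quantity, so both are assumptions. With π = 0.5 this becomes r/(r + 1).

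| Assumed r | Respondent prevalence | Bias (points) | Coverage of a nominal 95% interval at n = 796 |
|---|---|---|---|
| 1.10 | 52.4% | +2.4 | about 66% |
| 1.25 | 55.6% | +5.6 | about 5% |
| 1.50 | 60.0% | +10.0 | about 0% |

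The bias equals 3 points when r = 0.53/0.47 = 1.13. The sample size does not appear in the bias formula, so at a given r a larger n narrows the interval around the wrong value.

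**4. The same check by responder gap.** If 796 of 3,117 take part, bias = (1 − 796/3,117) × gap = 0.745 × gap, where the gap is the prevalence difference between responders and non-responders. Assumed gaps of 5 and 10 points give 3.7 and 7.4 points. Break-even with the 3-point margin is 3/0.745 = 4.0 points, and a smaller gap stays inside it.

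**The case against.** The strongest reply is that the article already discloses the weakness. It describes forwarding and snowballing openly, admits possible selection bias and limited representativeness, and calls its objectives exploratory. The primary objective is an association, with regressions adjusted for age, sex and occupational group; prevalence is only part of one secondary objective. All of that is fair, and it makes this largely a correction of claims. It does not remove the conflict: the generalization to CAM workers stands in the same section as the admission, and Conclusions then restates representativeness. Heterogeneity, the defence offered, is a different property. A sample can contain every job type and still over-represent staff in pain.

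Several stronger readings are tempting but unsupported:

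- *The sample size is wrong.* It is not; the arithmetic holds for the population it names.
- *±3% is claimed for the CAM.* The Sample Size section ties it to UAH. The uncorrected ±3.47%, or the 1,068 needed for ±3% without the correction, therefore rebuts no stated claim. Nor would a larger n make one university stand for the region.
- *Prevalence will be reported with an invalid interval.* Planned Data Analysis promises 95% intervals for regression coefficients and frequency distributions for categorical variables. No prevalence interval is promised.
- *Prevalence will be unweighted.* The article is silent, and a fuller plan may address weighting.
- *Referral or department clustering widens the margin by a known factor.* The article gives no design effect and lists neither department nor referral source among its sociodemographic variables.

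**Conclusion.** The point holds as a contradiction between what the article claims for its sample and what its recruitment can deliver. The ±3% margin is correct arithmetic for a simple random sample of 3,117 UAH staff; it does not bound the error of a volunteer sample and does not apply to the wider population named in the objectives. The consequence falls mainly on MSD prevalence. Under an assumed 50% prevalence, a participation ratio of about 1.13 is enough for a 3-point bias. The actual direction and size of selection are unknown, so this shows how fragile the stated precision is and is not an estimate of the bias. The association objectives are less exposed, although selection related to both activity and health could bias them too. A reader might infer that the survey is uninformative or that its associations are invalid; the document does not support going that far.

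**What to change.** 1. In Study Design, Study Population and Setting, and Conclusions, replace the population-based and representative descriptions with a self-selected sample of UAH staff.
2. Remove the generalization to the CAM working population, and limit prevalence conclusions to responding UAH staff.
3. In Sample Size, describe ±3% as a nominal planning figure under simple random sampling of UAH staff that excludes selection bias.
4. If aggregate UAH counts by staff category, sex and age can be obtained, compare respondents with the workforce and report MSD prevalence calibrated to those counts beside the crude figure, as a sensitivity analysis. State that calibration corrects imbalance on those three factors only. It does not remove self-selection on health, extend inference beyond UAH, or supply the inclusion probabilities that design-based intervals require.

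The cost is a less favourable statement of precision and reach, a request for aggregate counts (the article gives only the workforce total, so their availability is not assured) and one extra analysis. Age, sex and work role are already collected. Recruitment runs to June 2027 and the article reports no analyses to date, so the changes can be made before results are known.
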